## Abstract

**Background:**

Disadvantaged groups are an important target for smoking cessation intervention. Smoking rates are markedly higher among severely socially disadvantaged groups such as indigenous people, the homeless, people with a mental illness or drug and alcohol addiction, and the unemployed than in the general population. This proposal aims to evaluate the efficacy of a client-centred, caseworker delivered cessation support intervention at increasing validated self reported smoking cessation rates in a socially disadvantaged population.

**Methods/Design:**

A block randomised controlled trial will be conducted. The setting will be a non-government organisation, Community Care Centre located in New South Wales, Australia which provides emergency relief and counselling services to predominantly government income assistance recipients. Eligible clients identified as smokers during a baseline touch screen computer survey will be recruited and randomised by a trained research assistant located in the waiting area. Allocation to intervention or control groups will be determined by time periods with clients randomised in one-week blocks. Intervention group clients will receive an intensive client-centred smoking cessation intervention offered by the caseworker over two face-to-face and two telephone contacts. There will be two primary outcome measures obtained at one, six, and 12 month follow-up: 1) 24-hour expired air CO validated self-reported smoking cessation and 2) 7-day self-reported smoking cessation. Continuous abstinence will also be measured at six and 12 months follow up.

**Discussion:**

This study will generate new knowledge in an area where the current information regarding the most effective smoking cessation approaches with disadvantaged groups is limited.

**Trial registration number:**

ISRCTN: ISRCTN85202510

## Background

### The high burden imposed by smoking in socially disadvantaged groups

Quitting smoking is the single most important preventive health behaviour significantly reducing risk of morbidity and premature mortality [1]. Disadvantaged groups are an important target for smoking cessation intervention. Social disadvantage may be defined in terms such as low socioeconomic status or poverty, or less easily quantified indicators of deprivation such as not having adequate and affordable housing; or being subject to discrimination [2]. Smoking rates are markedly higher among severely socially disadvantaged groups than in the general population where rates are declining [1]. In Australia, smoking rates have been found to be highest amongst the following groups; Aboriginal and Torres Strait Islander people (50%), the homeless (70%), people with a mental illness (60%), people with drug and alcohol problems (74% to 100%), vulnerable youth (65%), those in prison (90%) and low-income single mothers [3-6]. These data reveal that the poorest and most marginalised members of society are the most likely to be smokers and at highest risk of smoking related disease.

### The personal and environmental context of smoking and quitting in disadvantaged groups

Qualitative research has shown that smoking is often deeply embedded in the lives of disadvantaged smokers because they live, socialise and/or work with other smokers, making it more difficult to refrain from smoking [7]. It has also been shown that smoking is influenced by unfavourable life trajectories such as childhood and educational disadvantages [8]. Smokers from more deprived socioeconomic groups also have higher levels of stress which can play a role in relapse because smokers often use smoking to cope with stressful aspects of their lives [9]. Importantly, studies have described the higher rates of nicotine dependence in smokers from more deprived socioeconomic groups [10], and past research has found nicotine dependence is a predictor of failure of attempts to stop smoking [11]. These factors suggest that smokers from lower socioeconomic groups may need strategies that address their unique life circumstances.

Studies have found that socially disadvantaged smokers are as interested in and as motivated to quit as other smokers [12,13]. However, some important differences in quitting behaviours between socioeconomic groups exist. Lower socioeconomic groups tend to receive less physician advice to quit, [14] access telephone quitlines less, even during mass media campaigns [15] and use fewer pharmacotherapies [16]. Also, although the number of quit attempts is similar across groups, it is achieving quitting success that is difficult for those in lower socioeconomic groups [17]. It appears smoking and smoking cessation in disadvantaged groups are complex behaviours with deeply embedded interacting influences. Multifaceted and intensive interventions addressing multiple motivators may be appropriate approaches for further research.

### Evidence regarding the effectiveness of smoking cessation interventions targeting the socially disadvantaged

The efficacy and effectiveness of a range of cessation interventions have been repeatedly and rigorously evaluated for the general population, including brief advice from health professionals, counselling, and pharmacotherapy [18]. However, there is a paucity of methodologically rigorous trials evaluating smoking cessation interventions among the socially disadvantaged. Three reviews [19-21] specifically targeting socially disadvantaged populations were unable to identify smoking cessation interventions with sufficient evidence supporting their efficacy or effectiveness in the groups examined. More recently, Murray et al [22] have reviewed the literature describing strategies to improve access to smoking cessation services for disadvantaged groups. Tailoring interventions and making them more 'client-centred', providing cessation support at accessible settings and using established cessation strategies improved proxy outcomes such as intention to quit and attitudes towards smoking. Although the overall trend of the results showed promise, the studies displayed several limitations such as small sample sizes, observational designs, use of proxy 'smoking behaviour and intent' outcomes and lack of biochemically verified smoking cessation outcomes [22].

### Community social service setting for reaching the socially disadvantaged

Non-government, community based social and welfare agencies are a suitable setting for reaching vulnerable sub-groups of the population. They access a high proportion of the groups with high smoking rates on a regular basis, are increasingly open to providing cessation support, are a trusted source of support and provide or liaise with a range of auxiliary support services that address additional life issues known to affect relapse [23]. In New South Wales (NSW) Australia, there are over 7,000 community service organisations assisting over 85,000 clients a year [23]. Clients include those most affected by smoking; low income families, the unemployed, Indigenous Australians, those with mental health concerns, marginalised youth and people with addiction problems. Overall, the services estimated that over half (56%) of their clients were current smokers [24]. Local cancer authorities have recognised the potential of this setting to reach disadvantaged smokers [3,25]. One study used a qualitative evaluation to test the potential of a smoking cessation group program in three community social services; a residential drug and alcohol treatment centre, an Aboriginal health service and a mental health service [25]. A key feature of the intervention involved the use of an algorithm allowing for individually tailored combinations of NRT for 'hard to treat' smokers [26]. The study, which was limited by a number of factors found high rates of smoking cessation (32% validated self report at 6 months follow-up) [25].

### Study Aims

This study aims to evaluate the efficacy of a client-centred, caseworker-delivered cessation support intervention at increasing smoking cessation rates in a socially disadvantaged population.

## Methods/Design

### Study Design

A block randomised controlled trial will be conducted. At baseline, clients attending one community social service will be asked to complete a touch screen computer survey asking them about health issues and their smoking status. Clients identified as smokers will be asked to participate in a smoking cessation trial. Allocation to the intervention or control groups will be determined by time periods with clients randomised in one-week blocks to reduce selection bias and contamination between groups. The trial has been carefully designed to conform to the CONSORT statement which has recently been updated for psychosocial and behavioural interventions [27].

The trial is funded by the National Health and Medical Research Council (NHMRC) of Australia (Ref no. 631055) and approved by the University of Newcastle Human Research Ethics Committee (Ref no. H-2010-1002).

### Setting

The study will be conducted in a non-government organisation, Community Care Centre (referred to here as the Centre) which is a community social service located in NSW, Australia providing financial counselling, relationship counselling, Life Skills courses, emergency relief and a communal use room/waiting area. The Centre operates 7 days a week, providing counselling services 4 days a week and predominantly assists those on government income assistance (95% of clients).

### Sample

Clients eligible for the trial will be those aged over 18 years, attending the Centre for their first visit, and who are self-reported smokers. Clients who have attended the Centre at another time in the past and are returning to start a new program will be eligible to participate. English-speaking clients who are unable to read at this level will be offered assistance from the research assistant (RA) to complete study consent forms and surveys. *Ineligible clients *will be those who are non-English speaking, presentation with uncontrolled mental illness (as identified by the RA and confirmed by the caseworker), and whose partner is already enrolled in the study.

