##### Use of effective cessation support strategies

A major component of the intervention is the *provision of pharmacotherapy. *Evidence suggests that smokers from lower socioeconomic backgrounds have higher levels of nicotine dependence [3] and that pharmacotherapy is an essential component of cessation care [11]. Clients will be offered a choice of medication at no cost. Nicotine replacement therapy almost doubles the chance of quit success compared with placebo [18]. A simple, safe and user-friendly version of the Bittoun [25,26] algorithm for appropriate use of multiple NRTs will be offered to clients with high nicotine dependence. Local pharmacists will also be provided with the algorithm and suggested as a source of advice and monitoring. There is evidence that the ability to quit smoking and maintain cessation is influenced by social support [18,46]. The case worker will ask the client to nominate a *'support' person *for their quit journey and provide a *support pack *to give to their support person. The support pack will contain advice on support strategies (e.g. advice on supportive behaviour, committing to an attempt to quit together until successful, not smoking near them, an NRT discount voucher if a smoker, and the Quitline number). If a client does not have a potential support person, the caseworker will locate a volunteer at the Centre who will take on the role of the support person via telephone contact.

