##### Support for other potentially relapse-related factors

Clients experiencing stressful situations (mental health, financial or relationship concerns), as recorded at the survey print-out will be offered enrolment into *Life Skills courses *provided by the Centre. Other support options in the local area will be discussed. There is evidence that individuals from lower socioeconomic positions tend to have greater needs for a variety of life stressors including housing needs, financial stress, employment concerns and physical and mental health concerns which affect relapse [9] They will also be offered the opportunity to schedule a visit together with their support person. At the final scheduled face to face meeting, clients will be asked to drop-in or phone-in when they require assistance. They will be told that their counsellor will make further phone contact to monitor progress and address relapse.

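### The enrolled-partner exclusion leaves out nominated non-partner support persons, who receive part of the intervention and can still be enrolled as controls

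*Protocol article*

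**What the plan says.** **Who may enter.** Under Sample, eligible clients are adults "attending the Centre for their first visit, and who are self-reported smokers", and past attenders starting a new program also qualify. Three groups are ineligible: non-English speakers, clients with uncontrolled mental illness, and anyone "whose partner is already enrolled in the study". Only the third concerns a link to another participant.

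**Whom the intervention reaches.** In Appendix 1, session 1 (Use of effective cessation support strategies), the client names a support person and is given a pack to pass on. The pack covers supportive behaviour, then "committing to an attempt to quit together until successful, not smoking near them, an NRT discount voucher if a smoker, and the Quitline number". Session 2 (Support for other potentially relapse-related factors) adds the offer of a visit made together with that person. Nothing limits the choice to a partner.

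**How arms are assigned.** Under Recruitment and randomisation, the research assistant approaches every client who enters, and the arm follows from the week of attendance. Study Design gives one-week blocks as the measure against selection bias and contamination.

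**The concern.** The article fixes an exclusion for linked people but draws it narrower than the links its own intervention creates. There are two routes into the control arm:

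- A smoking support person who is not the partner receives the pack, later becomes a Centre client in a control week, and is enrolled as an unexposed control.
- A client already enrolled as a control is named by an intervention client and then receives the pack.

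Overlap is plausible. There is one site, and the Background describes disadvantaged smokers as living and socialising with other smokers.

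Weekly allocation does not close either route. It keeps apart clients who attend in the same week, but not linked people who arrive in different weeks. Under The Case Worker Sessions, face-to-face visits are two weeks apart with phone contacts afterwards, so exposure outlasts a one-week block.

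At stake is a control arm in which some members have had part of the treatment. If that helps them quit, the difference between arms shrinks. This cannot be undone after enrolment.

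**Working it through.** **Inputs from Sample size:** control quit rate 5%, intervention 13%, 5% significance, 80% power, 200 per group at 12 months, 290 per group recruited, 60% consent. Sidedness is not stated; two-sided is used because it reproduces the plan's figure.

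**Step 1. Reproduce the plan's figure.** With p0 = 0.05, p1 = 0.13 and mean 0.09:

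n = [1.960 × √(2 × 0.09 × 0.91) + 0.8416 × √(0.05 × 0.95 + 0.13 × 0.87)]² / 0.08²
= (0.7932 + 0.3373)² / 0.0064 = 199.7, so 200 per group, as stated.

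Power at 200 = Φ[(0.08 × √200 − 0.7932) / 0.4007] = Φ(0.844) = 80.1%. There is almost no reserve.

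**Step 2. Dilute the control arm.** The exposed share f is not in the document, so 2% and 5% are assumed. If each exposed control gains the full effect, the control rate is 0.05 + 0.08f.

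| f (assumed) | Exposed of 290 | Control rate | Difference | Power at 200 per group | N per group for 80% |
|---|---|---|---|---|---|
| 0 | 0 | 5.00% | 8.00 points | 80.1% | 200 |
| 2% | about 6 | 5.16% | 7.84 points | 78.1% | 210 |
| 5% | about 15 | 5.40% | 7.60 points | 75.0% | 226 |

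**Step 3. Relax the full-effect assumption.** If the pack carried a quarter of the effect (assumption), the control rate is 0.05 + 0.02f. For f = 2% it is 5.04% and power is 79.6%; for f = 5% it is 5.10% and power is 78.9%.

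**Step 4. How many support persons would have to cross over?** Consider newly enrolled exposed controls only. Suppose half of weeks are control weeks (assumption) and 60% consent. Each such control then needs 1 / (0.5 × 0.6) = 3.3 eligible smoking, non-partner support persons coming to the Centre.

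- f = 2%: 5.8 / 0.30 = about 19, or 1 in 15 of the support persons of 290 intervention clients.
- f = 5%: 14.5 / 0.30 = about 48, or 1 in 6.

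Enrolled controls who are named as support persons would come on top of this.

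**The case against.** **The entry criterion filters the first route.** Definition of current smoker requires smoking in the past 7 days. A support person who has already quit cannot enrol, and one who does enrol is still smoking despite the pack. Such people might even quit less than other controls, so the direction of bias on this route is not certain. This stands, and it is one reason why the full 8-point gain is only an upper bound. It does not apply to a control who is named after enrolment.

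**The pack is not the intervention.** Support persons do not get free medication, a behavioural contract, a tailored checklist or phone follow-up, and controls already receive the Quitline number. This also stands. But advice to quit together and subsidised NRT are active elements that controls are not meant to receive.

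**The purpose of the partner rule is not given.** It may guard against correlated outcomes in couples rather than contamination. That is possible, but the gap for support persons exists under either reading.

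**Re-enrolment.** A reader might infer that a current participant can be allocated a second time, because "Clients who have attended the Centre at another time in the past and are returning to start a new program will be eligible to participate". The article does not support this. The sentence qualifies the first-visit criterion and says nothing about people already in the trial. A rule that each person enters once is ordinary detail that an article may leave to the full protocol.

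**Conclusion.** The gap is real but limited. As written, the article lets a non-partner support person who has received intervention material be enrolled as a control, and lets an enrolled control be named as a support person. The number affected cannot be derived from the document and is probably small.

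Under assumed shares of 2% to 5% and an upper-bound effect, power falls from 80.1% to between 78% and 75%; with a quarter of the effect it stays near 79% to 80%. A reader might take the range further and report power below 70% (69.5% at 10% exposed). That would need 29 exposed controls, each gaining the full effect. By the reckoning in Step 4, this means about 29 / 0.30 = 97 crossing support persons if all were newly enrolled, or one in three. Nothing in the document supports that.

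The sample size of 200 per group is not wrong and need not change. The case for acting is that an existing rule can be widened cheaply before recruitment.

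**What to change.** - **Sample:** extend the partner exclusion to anyone who has been named as a support person for an enrolled client. Apply it before allocation and identically in intervention and control weeks, so that the exclusion does not itself differ by arm.
- **Enrolled clients named later:** do not ban the nomination. A ban would alter an intervention component and could reveal to one client that another is in the trial. Record the nomination and its date, keep the client in the arm as allocated, and run a sensitivity analysis that takes these clients into account.

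**Cost.** One more screening check alongside the existing partner check, and a few lost recruits. Sample size expects 585 consenting clients against 2 × 290 = 580 needed, a margin of 5, although that count starts from new clients only while returning clients are also eligible. Support persons have not consented to the trial, so asking the client at screening is preferable to holding a list of named third parties.

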### Sample size

A sample of 200 participants per group at 12 months will allow detection of a difference in smoking cessation rates of 8% between groups at 12 months (slightly smaller difference of 7% can be detected at 1 month), based on 5% smoking cessation in the usual care group and 13% in the intervention group, at 5% significance level and 80% power. This effect size is achievable and important from a population-effect perspective. Non-randomised and observational studies using less intensive smoking cessation interventions within disadvantaged groups have demonstrated high cessation rates [25,28-30]. Estimating that 30% of the sample are lost to follow-up (10% at each of one, six and 12 months), 290 patients per group will be recruited at baseline. The Centre receives approximately 50 new clients a week and 50% of those are for ongoing counselling care. All new clients will be eligible to complete the baseline touch screen computer survey. Over a 12-month recruitment period, 1,300 new clients will attend for counselling services. Staff estimate that 60%-90% of clients are current smokers. Assuming a median value of 75%, there will be approximately 975 eligible clients during the study period. Assuming a consent rate of 60% [28-31], 585 individuals will consent to participate in the study.

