### Recruitment and randomisation

A trained RA will be situated in the Centre communal waiting room during recruitment. The RA will approach all clients entering the Centre, ascertain eligibility, and seek written consent. A two-stage consent process will be used. First, the RA will inform clients that the study aims to expand the services provided by the Centre and involves completing a health survey on a touch screen computer and that their case-worker may discuss health issues with them. When they complete the survey, if they reported to smoke, they will be informed, on-screen, that a study for smokers is being conducted and that the RA will seek their consent to participate in the smoking study. They will be told that participation in the smoking study will involve their counsellor or case worker possibly discussing quitting with them, and that they will be asked to return to the Centre in one, six and 12 months time to complete the survey and conduct a breath test for carbon monoxide (CO) measurement. Consenting clients will be assisted in the use of the touch screen survey. The RA will review the clients' smoking status on a touch screen survey print-out and randomly allocate participants who are current smokers to the control or intervention group depending on whether it is an intervention or control week. Intervention or control times will be randomly allocated in blocks of four by a computer generated randomisation procedure. Clients who are not smokers will not participate further in the study.

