#### Efficacy of intervention

To assess the efficacy of the intervention at smoking cessation (validated by expired air CO), the intervention and control groups will be compared on each of the primary outcomes using chi-square analysis: 1) proportion abstinent last 24 hours (validated) at one, six and 12 months; and 2) proportion abstinent for seven days at one, six and 12 months. Univariate analyses will be undertaken to examine factors associated with each of the two outcomes, using the chi-square test for categorical variables and the t-test or a non-parametric equivalent for continuous variables. In addition to the primary analysis, intention-to-treat analysis will also be undertaken whereby clients who fail to complete follow-up in the study will be considered to be continuing smokers. Multiple logistic regression analyses will be used to compare outcomes between the two intervention groups while adjusting for prognostic variables and potential confounders (sociodemographic, financial stress, depression, and other variables collected).

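### Weeks are randomised, but the sample size and the primary chi-square test treat clients as independent, so the stated 80% power and 5% significance level are not assured

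*Protocol article*

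**What the plan says.** The Study Design section states: "Allocation to the intervention or control groups will be determined by time periods with clients randomised in one-week blocks". Under Recruitment and randomisation, the research assistant places a smoker in an arm "depending on whether it is an intervention or control week", and "Intervention or control times will be randomly allocated in blocks of four by a computer generated randomisation procedure". No step randomises an individual client.

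The Sample size section states: "A sample of 200 participants per group at 12 months will allow detection of a difference in smoking cessation rates of 8% between groups". The figure is "based on 5% smoking cessation in the usual care group and 13% in the intervention group", "at 5% significance level and 80% power". It names no ICC, design effect or number of weeks. Recruitment is set at 290 per group over 12 months to allow for 30% loss, and 585 consenting clients are forecast.

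Under Efficacy of intervention, "the intervention and control groups will be compared on each of the primary outcomes using chi-square analysis". A multiple logistic regression then adjusts for client-level prognostic variables and confounders.

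**The concern.** All clients recruited in one week receive the same arm, so the week is the randomised unit and the trial is cluster randomised in time. A two-group chi-square test and its sample size formula both take each client as an independent draw. If clients recruited in the same week resemble one another more than clients from different weeks do, the variance of the difference between arms is larger than either assumes.

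At stake is the validity of the primary p-value or, once the analysis is corrected, the power on which the trial was sized. The article fixes both the sample size and the primary test, so this is not a detail left to an unseen analysis plan.

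**Working it through.** **Inputs from the article:** 5% v 13% cessation; 5% significance level; 80% power; 200 evaluable and 290 recruited per group; 30% loss; 12-month recruitment; weekly allocation in blocks of four.

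**Assumptions:** a two-sided test (this reproduces the stated figure); 52 recruiting weeks, about 26 per arm; weeks of equal size in the formulas; blocks of four weeks split 2:2; ICC varied, because the article gives none.

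**1. The stated figure.** Pooled two-proportion formula without continuity correction, mean rate 0.09:

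n = [1.96 × √(2 × 0.09 × 0.91) + 0.8416 × √(0.05 × 0.95 + 0.13 × 0.87)]² / 0.08²

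= [1.96 × 0.4047 + 0.8416 × 0.4007]² / 0.0064 = 199.7 per group.

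Power at 200 per group is 80.06%. The stated 200 is thus the individually randomised answer, with nothing added for clustering.

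**2. Cluster size.** 400/52 = 7.7 evaluable clients per week (580/52 = 11.2 recruited).

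**3. Effect of week-specific correlation.** Design effect DE = 1 + (7.7 − 1) × ICC; effective n = 200/DE; type I error of the unadjusted test = 2 × [1 − Φ(1.96/√DE)].

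| Assumed ICC | DE | Effective n per arm | Power, valid week-aware test | Type I error, planned chi-square |
|---|---|---|---|---|
| 0 | 1.000 | 200 | 80.1% | 5.0% |
| 0.01 | 1.067 | 187.5 | 77.5% | 5.8% |
| 0.02 | 1.134 | 176.4 | 74.9% | 6.6% |
| 0.05 | 1.335 | 149.9 | 67.9% | 9.0% |

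A beta-binomial simulation (26 weeks per arm, Poisson week sizes, 20,000 replicates) gave chi-square type I errors of 5.8%, 6.7% and 9.1% at the three positive ICCs, and 4.9% at ICC 0.

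**4. The two columns are alternatives.** Under 5% v 13%, the planned chi-square still rejected in 80.5%, 79.8% and 77.3% of simulated trials at these ICCs (81.2% at ICC 0). Its main defect is the false-positive rate. The lower powers belong to a test that restores the 5% level.

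**5. Effect of the blocking.** In a further null simulation (52 weeks in 2:2 blocks of four, 5% rate, 7.7 clients per week, 20,000 replicates), the chi-square type I error at ICC 0.01, 0.02 and 0.05 was:

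- all correlation week-specific: 5.7%, 6.6%, 9.5%
- half shared within the block: 5.4%, 5.8%, 6.8%
- all shared within the block: 5.0%, 4.9%, 5.1%

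The type I errors in the table are therefore the upper end of a range that starts at about 5%.

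**6. Reserve in the plan.** 290 × 0.70 = 203 evaluable per group, and 203/200 = 1.015, which covers an ICC of about 0.015/6.7 = 0.002. The forecast of 585 consenting clients exceeds the 580 needed by five.

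**The case against.** The strongest reply is that the article does not show any within-week correlation. It mentions no benefit-payment cycle and no weekly caseworker roster, only that 95% of clients receive government income assistance. It describes the research assistant in the singular, and one assistant for all weeks adds no variation between weeks. Partners of enrolled clients are excluded, which removes one source of similarity. Caseworker contact runs on for weeks after recruitment. Slow influences such as season fall on both arms within a block and largely cancel. Weeks are small, so even an ICC of 0.01 costs only about 2.5 points of power or 0.8 points of type I error.

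All of this stands and limits the size of the point. It does not remove the mismatch: the chi-square is valid for this allocation only if week-specific correlation is absent, and the article neither states nor supports that assumption.

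It is also fair to say that an analysis plan could still specify the variance for the adjusted logistic model. The point therefore rests on the sample size and the named primary test, not on that model.

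**Conclusion.** The primary analysis and sample size do not match the randomisation. The stated 80% power and 5% level hold if there is no week-specific correlation and are otherwise not assured. For assumed week-specific ICCs of 0.01 to 0.05, either a valid week-aware test has 77.5% to 68% power, or the planned chi-square has a type I error of up to 5.8% to 9.0%. These figures rest on about 52 weeks of equal size and on an ICC range that is assumed throughout. To the extent that the correlation is shared within randomisation blocks, the losses fall towards zero, for power provided the analysis also uses the block.

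A reader might infer more than the article supports in three ways:

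- **That the stated figures are certainly missed.** This needs a positive week-specific ICC, which the article does not document.
- **That the trial loses power and also has an inflated error rate, each by the amount in the table.** The two columns describe different tests.
- **That 200 or 290 is miscalculated.** As an individually randomised calculation, 200 is exact, and 200/0.70 = 286 is close to the stated 290.

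**What to change.** 1. Describe the trial as cluster randomised by week.
2. Replace the client-level chi-square with a week-aware primary analysis, such as a logistic GEE with week as the cluster and small-sample-corrected robust errors, or a logistic model with a random week intercept. Use the same structure in the adjusted logistic model.
3. Account for the randomisation block without fixed strata. About 10 control-arm quitters are expected (5% of 200) over 13 four-week blocks, or 0.77 per block, so roughly 46% of blocks (e^−0.77) would have none. A random block effect or a permutation test restricted within blocks avoids this sparseness.
4. Restate the power with an assumed ICC and its range: about 75% at ICC 0.02, and 68% to 78% for ICC 0.05 to 0.01.

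The cost is revised wording, a slightly more complex analysis and a slightly less favourable stated power, with no extra participants. Holding 80% power instead would take about 305, 324 or 382 recruits per arm at ICC 0.01, 0.02 or 0.05, which is more than the forecast of 585 in total. The choice of method should be fixed before outcomes are seen.
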